##### 2.1.2.3 Recruitment and grouping of participants

This study employed a multi-faceted recruitment strategy that integrated hospital-based and online channels to enroll pregnant women. Announcements regarding the clinical trial were disseminated via the WeChat official account of the Inner Mongolia Maternal and Child Health Hospital and associated collaborative medical institutions, with an electronic questionnaire QR code appended to the posts. Pregnant women and their families interested in participation were able to provide their contact details through the electronic questionnaire, after which they were contacted by study staff for further coordination.

Furthermore, outpatient surveys conducted at the Inner Mongolia Maternal and Child Health Hospital identified pregnant women presenting for check-ups or consultations with obesity-related symptoms. For those who expressed interest, a questionnaire survey was administered by the outpatient healthcare providers.

### 2.2 Randomization

After recruitment, the research team will conduct a pre-enrollment assessment and post-enrollment informed consent with the participants and their families, followed by randomization grouping:

A comprehensive assessment will be conducted before the participants are enrolled, including structured questionnaires and clinical examinations.

The approved subjects were randomly divided into Manual intervention group, artificial intelligence intervention group (AI intervention group), artificial intelligence and artificial combined intervention group (AI & Manual intervention group). The specific randomization operation is as follows: This study uses a simple randomization method. Random number series were randomly generated by the study designer using the RANDBETWEEN formula in EXCEL. The project will divide the subjects into different groups according to the sequence, the intervention team will know the grouping results, and the subjects will not know the grouping results.

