#### 2.1.1 Sample size

As this study is a randomized controlled trial, the respondents will be divided into manual intervention group, artificial intelligence (AI) intervention group, artificial intelligence and manual combined intervention group, and observe the BMI of pregnant women, maternal weight and maternal adverse pregnancy outcomes as the main outcome indicators. The sample size was calculated based on an expected effect size of 0.5, which corresponds to the minimal clinically important difference (MCID) of the primary outcome. This MCID was determined based on previous literature and clinical judgment. Setting bilateral α = 0.05, the degree of certainty was 90%. Using the PASS15 software, we obtained a sample size of N1 = 40 cases for the group and N2 = 40 cases for the group and N3 = 40 cases for the group. For a total of at least 120 subjects to be included in the study.

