Next are the differences with the existing literature. Notably, our cost-benefit analysis revealed that the AI-only intervention offered a scalable solution with moderate efficacy, whereas the combined AI+Manual group achieved the highest clinical impact. This contrasts with Perdomo et al., who emphasized surgical and pharmacological interventions as primary strategies for severe obesity (15). However, our results align with Sallam et al., where TLC combined with medication synergistically improved metabolic outcomes (20). Such parallels suggest that hybrid models (AI + human expertise) may bridge the gap between resource-intensive and purely automated interventions.

However, this study has the following limitations. First, despite the high coverage rate of smartphones in China, some patients may not be able to use them well, which may hinder the implementation and reduce the effectiveness of AI interventions. Second, for the collection of the primary and secondary outcomes, we primarily used questionnaire indicators, which may inevitably lead to recall bias. Third, due to the lack of balanced stratification, comparative analyses between subgroups may not be suitable if the sample size of each group is insufficient across groups (e.g., compare the differences and potential influencing factors of AI-TLC intervention effects in different age groups). Fourth, the short-term follow-up period (up to 3 months postpartum) precludes conclusions about long-term weight maintenance. Meta-analyses of lifestyle interventions for obese pregnant women indicate that postpartum weight retention remains a challenge beyond 12 months (35), emphasizing the need for extended follow-up in future studies. Additionally, socioeconomic disparities in AI accessibility—particularly among older or rural populations—may limit generalizability, necessitating stratified analyses in broader cohorts.

Despite these limitations, this study may provide a scientific basis for developing personalized and effective interventions to further improve the health behavior and health of obesity pregnant women. It is expected to provide a new perspective and effective approach to the management of obesity pregnant women.

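### Simple, unstratified randomisation is a poor match for the stated 40/40/40 and leaves balance in the planned age and BMI-class subgroups uncontrolled

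*Protocol article*

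**What the plan says.** Protocol article, section 2.2: "This study uses a simple randomization method. Random number series were randomly generated by the study designer using the RANDBETWEEN formula in EXCEL". Women are placed in the three arms in the order of that series, after assessment and consent. The section mentions neither blocks nor strata. On knowledge of the assignment it says that "the intervention team will know the grouping results, and the subjects will not know the grouping results".

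Section 2.1.1 gives the target as "N1 = 40 cases for the group and N2 = 40 cases for the group and N3 = 40 cases for the group" and adds: "For a total of at least 120 subjects to be included in the study".

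Sub-question 1 in the Introduction asks whether the effect varies with age and degree of obesity. Section 2.4.2 plans subgroup analyses by age and BMI class with interaction tests, and section 2.6 adds subgroups by socioeconomic status. The limitations in section 3 Discussion then say that "due to the lack of balanced stratification, comparative analyses between subgroups may not be suitable". The sentence makes this conditional on group sizes being too small and gives age groups as its example.

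**The concern.** Two stated choices pull against each other. The sample size section fixes three equal arms, but independent draws do not produce equal arms except by luck. The plan also makes effect differences by age and degree of obesity a named question, yet randomises without regard to either, and its own limitations section points to that as a weakness.

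At stake are some precision in a small trial and the usefulness of the subgroup comparisons. This is not detail that an article leaves to a fuller document: simple randomisation is stated outright and the lack of stratification is acknowledged.

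**Working it through.** **1. The plan's own figure.** Section 2.1.1 says "The sample size was calculated based on an expected effect size of 0.5", with two-sided α = 0.05 and 90% power. Read as a standardised difference between two means, n = 2 × ((1.960 + 1.282) / 0.5)² = 84.1, so 85 per arm (86 by the t-test). A three-group ANOVA needs 18 per arm at f = 0.5 and 69 at f = 0.25. None of these gives 40, which needs an unstated input such as f of about 0.33. That is a separate matter; below, 40 per arm is simply taken as the stated target.

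**2. Chance of 40/40/40.** Inputs: N = 120 (section 2.1.1) and probability 1/3 per arm (implied by the equal targets). The multinomial probability is 120! / (40!³ × 3¹²⁰) = 0.00685, or 0.7%. If the arms are not all 40, at least one is below 40, so that has probability 1 − 0.00685 = 99.3%.

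**3. How unequal.** The SD of one arm is √(120 × 1/3 × 2/3) = 5.16, with a 95% range of 30 to 50. Exact enumeration over all splits of 120 gives:

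| Quantity | Result |
|---|---|
| Expected smallest / largest arm | 34.7 / 45.4 |
| Expected gap, largest minus smallest | 10.7 |
| Chance of a gap of 10 or more | 54% |
| Median smallest arm | 35 |
| Chance smallest arm is 35 or fewer | 55% |
| Chance smallest arm is 33 or fewer | 30% |

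**4. If more than 120 are enrolled.** The text gives 120 as a minimum. By simulation, the chance that every arm reaches 40 under simple randomisation is 33% at 130 women, 71% at 140, 90% at 150 and 95% at 155.

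**5. Cost in power.** Two-sample t-test, standardised difference 0.5, two-sided 0.05, no covariate adjustment:

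- 40 v 40: 59.8%.
- Any given pair, averaged over the arm sizes in step 3: 59.2%, a loss of 59.8 − 59.2 = 0.6 points.
- The two smallest arms, averaged likewise: 56.4%, a loss of 59.8 − 56.4 = 3.4 points.

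**6. Subgroups.** The article gives no subgroup sizes, so these are assumed. The chance that, within the subgroup, the largest arm is at least twice the smallest is:

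| Subgroup size (assumed) | Chance |
|---|---|
| 20 | 48% |
| 30 | 33% |
| 40 | 22% |
| 60 | 10% |

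**7. With blocks.** Unstratified blocks of 6 give 120 / 6 = 20 complete blocks, hence exactly 40/40/40. In an unfinished block of 6 the arms differ by at most 2, so with four strata the overall gap is at most 4 × 2 = 8. By simulation with four strata of equal expected size (assumed), the mean gap is 2.1, against 10.7 under simple randomisation, and the smallest arm is 38 or more in 98.5% of runs.

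**The case against.** Simple randomisation is a valid method. Arm sizes and subgroups balance in expectation, and step 5 shows that unequal arms cost little. The 0.7% applies to exactly 120 women, while the text sets a minimum. Baseline differences are partly handled in analysis: section 2.4.2 adjusts secondary outcomes for age and baseline BMI, and the GEE model in section 2.6 includes baseline as a time point. Stratifying does not enlarge a subgroup, so the main limit on interaction tests at this size stays. All of this stands, and it limits the weight of the point. It does not remove it: the article states no allowance for enrolling about 150, and even spread across arms is more secure by design than by later adjustment.

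A reader might go further and infer that allocation is unprotected, because the study designer made the list and the intervention team knows the groups. The article does not support that. It nowhere says that those who recruit can see the list. It puts assessment and consent before assignment. Staff who deliver the arms must know them afterwards. Under simple randomisation past assignments say nothing about the next. Custody of the list and the way assignments are released are details an article may leave to the full protocol. All that can be said is that concealment is not described.

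A reader might also take the limitations sentence as an admission that the subgroup comparisons are invalid, or conclude that subgroups will be unbalanced. The sentence is conditional on group size, and marked imbalance is likely only in small subgroups.

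**Conclusion.** The point holds as a matter of design efficiency. As written, the randomisation will almost certainly not yield the stated 40 per arm at 120 women, and a gap of 10 or more is slightly more likely than not. It leaves balance uncontrolled in the age and BMI-class subgroups that the plan names as a question of interest, and the authors acknowledge that lack of stratification as a possible problem if groups are small.

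The harm is modest: about 0.6 points of average pairwise power and about 3 for the two smallest arms. The arm-size results assume exactly 120 women and equal allocation probabilities, the power results a standardised difference of 0.5 with no adjustment, and the subgroup results assumed sizes. No dropout is applied. The change is worth making because it is cheap, not because the current method is invalid.

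**What to change.** Replace simple randomisation with permuted blocks of randomly varying size, in multiples of 3, stratified by pre-pregnancy BMI class. Add a two-level age group only if the strata stay large enough. Include the strata in the main GEE model. Have someone outside recruitment and intervention generate the list and hold it as fixed values, and add a sentence saying how each assignment is released.

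The BMI-class boundary depends on the entry threshold, which the abstract gives as 30.0 kg/m² and section 2.1.2.1 as 28.0 kg/m². Those passages must be reconciled first.

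The cost is about an hour to make the list, plus one existing team member to hold it. The downside is that blocks make some late-in-block assignments slightly more guessable to unblinded staff; varying, undisclosed block sizes limit this but do not remove it. If simple randomisation is kept, the plan should state an enrolment of about 150 for a 90% chance of 40 in every arm, which costs far more than changing the list. If recruitment has begun, apply the change to the remaining women and report it.

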### 2.3 Interventions

This study employs a therapeutic lifestyle changes (TLC) intervention to address the health behaviors of obesity pregnant women. The TLC strategy is comprehensive, encompassing three primary components: behavioral modification, dietary adjustments, and physical activity promotion, all facilitated by a multidisciplinary team comprising physicians, health managers, and nutritionists. Behavioral interventions involve advising patients to maintain daily records of weight, diet, and physical activity, to avoid prolonged sedentary behavior, to establish regular sleep patterns, to control eating pace, to ensure adequate hydration, and to reduce the frequency of dining out. Additionally, patients are encouraged to seek support from family and social networks and to engage in professional weight management education when required.

The dietary intervention is based on evidence-backed dietary patterns, including calorie restriction, very low-calorie diets, low-carbohydrate diets, high-protein diets, and intermittent fasting, all aimed at achieving a negative energy balance. Exercise guidance is tailored to the individual's health status and preferences, with recommendations developed under the supervision of qualified medical or fitness professionals. Psychological support is also integrated to bolster self-efficacy, mitigate stress, and alleviate symptoms of depression and anxiety, thereby enhancing the overall efficacy of the weight management program and improving the quality of life.

The fasting protocol in this study is structured as time-restricted eating (TRE), which limits food intake to an 8-h window each day, allowing for a 16-h fasting period. Participants are provided with detailed dietary guidelines that emphasize nutrient-dense foods, including adequate protein, healthy fats, and complex carbohydrates, to meet the increased nutritional needs during pregnancy. Regular monitoring of maternal weight gain and key health parameters, such as blood glucose and blood pressure, was conducted to ensure that fasting did not negatively impact maternal and fetal health. This helped in early detection and correction of potential nutritional deficiencies or excesses. Additionally, participants received education on healthy eating and lifestyle choices, emphasizing the selection of nutrient-dense foods during fasting and the avoidance of high-sugar, high-fat, and high-sodium foods to maintain a healthy weight and metabolic balance (26).

The research design incorporates a single-blind experimental setup, wherein participants are unaware of their allocation status or the identity of the intervention provider.

The Manual intervention group receives personalized TLC plans developed by the multidisciplinary team based on individual health profiles. The AI intervention group follows plans generated by an artificial intelligence algorithm using the same health data. The Combined intervention group benefits from a hybrid approach, where AI-generated plans are supplemented with expert recommendations from the healthcare professional team.

This study's methodology aligns with the rigorous standards expected by academic journals, ensuring a controlled and systematic evaluation of the TLC intervention's impact on health behaviors and outcomes among obesity pregnant women (Figure 2).

**Figure 2 F2:**
[figure not shown]
Therapeutic lifestyle changes (TLC) intervention.

### 2.4 Outcomes

#### 2.4.1 Primary outcomes

The primary outcomes of the study include maternal body mass index (BMI), maternal weight, and adverse pregnancy outcomes. The primary outcome measures (such as BMI, maternal weight, and adverse pregnancy outcomes) will be assessed using Repeated Measures ANOVA or Mixed Effects Models to evaluate the intervention effects. For long-term effect analysis, Generalized Estimating Equations (GEE) or Cox Proportional Hazards Models will be employed to assess the short-term, medium-term, and long-term impacts of the interventions. Cost-effectiveness analysis will be conducted using Quality-Adjusted Life Years (QALY) and Incremental Cost-Effectiveness Ratios (ICER) to evaluate the economic efficiency of different intervention measures, with sensitivity analysis performed to verify the robustness of the results.

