In China, patients with obesity and chronic diseases face severe challenges. Internationally, interventions for patients with obesity and chronic diseases are often supported by professional medical teams and community health programs. In contrast, Chinese patients tend to rely on hospitals and themselves. In view of China, therapeutic lifestyle intervention combined with AI technology, as an innovative intervention, is easy to implement and cost-effective. Through AI technology, personalized lifestyle advice can be provided, monitoring patient health data and timely adjusting treatment options. This intervention not only facilitates patients to receive management at home, but also can deliver professional support to meet the needs of patients in the process of lifestyle change effectively and efficiently. Therefore, research targeting this area has important practical significance and urgency.

This study designed a randomized controlled study to propose an AI-driven therapeutic lifestyle change (AI-TLC) intervention. Through personalization, continuous tracking feedback, intelligent decision aid, evaluate the influence of AI-TLC intervention on health behavior and health outcomes of obese pregnant women, determine the applicability and universality of AI-TLC intervention, provide innovative, efficient, and personalized health intervention for obese pregnant women, and provide new perspectives and methods for related scientific research and clinical practice.

Specific objectives are:

Primary: Can the intervention program driven by artificial intelligence (AI)–facilitated therapeutic lifestyle changes effectively promote improvements in health behaviors and health outcomes among pregnant women who are overweight or obese?

Sub-question 1:

Do the effects of the intervention differ among pregnant women of varying ages and degrees of obesity?

Sub-question 2: From a cost-benefit perspective, which level of intervention is the most effective (human-only vs. AI-only vs. human + AI)?

Sub-question 3: What are the short-term, medium-term, and long-term effects of this intervention program? What mechanisms need to be added to achieve better long-term outcomes?

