### 2.6 Statistical analysis

Participants' socio-demographics are presented as count and proportion, and the χ^2^ test was used to assess categorical variables. The continuous variables normally distributed were assessed by the student's *t*-test. The Fisher's exact or the chi-square test was adopted for categorical data, and statistical significance was set at *p* < 0.05. The main analysis was performed using generalized estimating equations (GEE) model. The GEE solved the problem of correlation of longitudinal data, utilizing the results of each measurement in the longitudinal data, which greatly reduces the loss of information (20). To clarify whether socioeconomic status affects the effectiveness of ILSM, we conducted several subgroup analyses for physiological health outcomes and health behaviors, and added the interaction terms to generalized estimating equations model to assess the interactions between time (at baseline, 3-month, 6-month, and 18-month) and group (intervention and control). We also used GEE to analyze the health benefits of intervention and control groups among participants with different socioeconomic status. Significance level of the associations in the final model was set at *P*-value 0.05. The data were analyzed using SPSS 20.0 (IBM Corporation, Armonk, NY, USA).

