## 3 Discussion

The rising prevalence of obesity among Chinese pregnant women, as highlighted in the introduction (29). In a physical examination data based on 15.8 million adults, according to the Chinese standard (overweight BMI ≥ 24, obese BMI ≥ 28): the overweight rate is 34.8% and the obesity rate is 14.1%. Among the obese, 81.8% suffered from fatty liver, 36.9% had hypertension, and 42.4% had dyslipidemia (30). Consequently, there is an urgent need for healthcare interventions to both prevent and manage the development of obesity and its associated complications. Our study demonstrates that the AI-TLC intervention significantly improved maternal BMI and reduced adverse pregnancy outcomes compared to manual-only approaches. These findings align with prior research on technology-driven interventions. For instance, Ferrara et al. reported a 6-month BMI reduction of −0.9 ±1.5 in an mHealth-based intervention for gestational weight management (31), suggesting that digital tools can effectively support behavioral modifications. Similarly, our observation that the combined AI+Manual group outperformed standalone interventions echoes studies on hybrid models, where human-AI collaboration enhanced both adherence and personalization (23). Recent advances in AI interventions provide an appealing and cost-effective approach to intervention targeting the improvement of health outcomes for obese patients with other chronic disease comorbidity (30). To date, studies in Chinese obese patients with other chronic disease comorbidity have not been reported.

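### Three unranked primary outcomes in three arms at a flat 0.05, with conflicting primary models: the chance of a false primary claim is about 10% to 25% depending on the unstated tests, and the Discussion already reports results

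*Protocol article*

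**What the plan says.** - **Primary outcomes.** Section 2.4.1: "The primary outcomes of the study include maternal body mass index (BMI), maternal weight, and adverse pregnancy outcomes". Section 2.1.1 lists the same three as the main indicators. Neither section ranks them, requires all of them to succeed, or gives another success rule.
- **Sample size.** Section 2.1.1 ties the effect size of 0.5 to the "minimal clinically important difference (MCID) of the primary outcome", in the singular, without saying which outcome. Alpha is two-sided 0.05, power 90%, and 40 women are planned per arm.
- **Arms.** There are three. Sub-question 2 in the Introduction asks "which level of intervention is the most effective (human-only vs. AI-only vs. human + AI").
- **Analysis level.** Section 2.6: "Significance level of the associations in the final model was set at *P*-value 0.05". No split, hierarchy or adjustment is given.
- **Model.** Section 2.4.1 assigns the primaries to repeated measures ANOVA or mixed effects models, and assigns GEE or Cox models to long-term effects. Section 2.6 makes GEE the main analysis, with a time-by-group interaction in which group means intervention and control.
- **Results.** The Discussion states: "Our study demonstrates that the AI-TLC intervention significantly improved maternal BMI and reduced adverse pregnancy outcomes compared to manual-only approaches". Later it says that "our cost-benefit analysis revealed that the AI-only intervention offered a scalable solution with moderate efficacy". The abstract puts recruitment and evaluation in the future and calls the findings anticipated.

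**The concern.** With three primaries, three arms and no success rule, the article leaves open which result would decide the trial. Any significant outcome could be presented as the primary result, so the error rate of the primary claim is not held at the 5% that the plan states. Listing both weight and BMI adds a second route to significance but almost no new information. Because the sample-size outcome is not identified, a reader cannot tell which claim the design was built to support.

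The result statements raise a separate problem. A protocol that reports significance cannot be read as a prospective plan until the contradiction is resolved.

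**Working it through.** **1. Stated figures.** The article gives no family-wise error rate to reproduce. Its only related figure is the sample size. With a standardized difference of 0.5, two-sided 0.05 and 90% power, n per arm = 2 × (1.960 + 1.282)² / 0.5² = 84.1, so 85, against 40 planned. Forty per arm gives about 60% power in a simple two-arm comparison. That shortfall is a separate matter; the 60% is used below only as the starting point for the cost of the fix.

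**2. Weight and BMI.** Change in BMI = change in weight / height². Height is fixed within a woman, so BMI change carries no information beyond weight change. Across women the divisor varies a little. With an assumed mean height of 160 cm (SD 5.5) the two changes correlate at 0.99. The range 0.97 to 0.99 is used here.

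**3. Chance of at least one false primary claim.** The setting is three equal arms with no true differences, normal test statistics, and any significant primary outcome counted as success. A pairwise test rejects when |X_i − X_j| / √2 > 1.96. An omnibus test rejects when Σ(X_i − mean)² > 5.99 (chi-squared, 2 df). The correlation of weight and BMI with adverse outcomes is assumed to lie between 0 and 0.5. Simulation gives:

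| Testing scheme | Chance of a false claim |
|---|---|
| One outcome, pairwise tests only after a significant omnibus test | 5.0% |
| One outcome, three unadjusted pairwise tests | 12.2% |
| Three outcomes, one contrast each | about 10% to 11% |
| Three outcomes, one omnibus test each | about 10% to 11% |
| Three outcomes, pairwise tests only after omnibus | about 10% to 11% |
| Three outcomes × three unadjusted pairwise tests (nine tests) | about 23% to 25% |

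A hand check treats weight and BMI as one outcome, independent of adverse outcomes. One test per outcome gives 1 − 0.95² = 9.75%. Three pairwise tests per outcome give 1 − (1 − 0.122)² = 22.9%. Both agree with the lower ends of the ranges.

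Widening the weight–BMI correlation to 0.80 to 0.9999 moves the omnibus figure to 9.2% to 12.6% and the nine-test figure to 21.5% to 28.3%. Multiple visits and the choice between models are not counted.

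**4. Primary model.** Section 2.4.1 offers two models for the primary outcomes, and GEE is not one of them. Section 2.6 names GEE as the main analysis. Section 2.6 also describes two groups, while sections 2.1.1 and 2.2 define three and designate none as control. These texts cannot all be followed.

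**5. Status of the trial.** The abstract says that the trial will recruit and will evaluate. The Discussion says that AI-TLC significantly improved BMI and reduced adverse outcomes, that the combined arm did best, and that a cost-benefit analysis produced a result. Both cannot be true of the same trial at the same time.

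**The case against.** Multiplicity adjustment and the choice of contrasts are often left to the analysis plan, which is not shown, and this is a condensed article. That stands: the absence of an adjustment method is a weak ground by itself. It does not cover what the article itself fixes badly, namely three unranked primaries, a sample size for an unidentified one, and two sections that disagree on the primary model.

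A reader might infer that nine pairwise tests are each run at 0.05, so that the error rate is simply 25%. The documents do not support this. No section lists pairwise tests. They can be inferred from sub-question 2 and from the arm comparisons in the Discussion, but ANOVA would normally start with an omnibus test, and section 2.6 as worded has a single intervention-versus-control contrast. Under those readings the figure is about 10% to 11%.

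A reader might also take GEE or Cox as further alternatives for the primary analysis in section 2.4.1. That section reserves them for long-term effects; the real conflict is with section 2.6.

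Finally, a reader might infer from the Discussion that outcome data have already been examined. That is speculative. Past tense is mixed into the methods too (eligibility, exclusions, recruitment, statistical analysis), so careless drafting is an equally good explanation. The contradiction needs correcting whichever is true.

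**Conclusion.** The concern holds in a conditional form. The article names three primary outcomes without rank or success rule, two of them one measurement, and does not say which one the sample size serves. Sections 2.4.1 and 2.6 conflict on the primary model and on the number of groups.

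If any significant primary outcome counts as success, the chance of a false primary claim exceeds 5% under every three-outcome scheme considered. It is about double the nominal level with one omnibus test, omnibus-gated tests or one contrast per outcome, and about 23% to 25% with unadjusted pairwise testing. The success rule, the testing scheme and the correlations are assumptions, because the article states none of them.

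Separately, and without any statistical assumption, the result statements in the Discussion contradict the abstract. The documents do not show that data were seen.

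**What to change.** (a) Name one primary outcome, for example baseline-adjusted weight at one stated visit from the schedule in section 2.1, and say that the sample size refers to it. Make BMI descriptive and adverse pregnancy outcomes secondary. The visit is the sponsor's choice; what matters is that one is fixed.

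(b) State the confirmatory contrasts and control them at two-sided 0.05. One option is an omnibus three-arm test followed, if significant, by the three pairwise tests. With three arms this is a closed procedure; it holds the error at 5.0% in the check above and keeps all the comparisons of sub-question 2. Holm is an alternative.

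(c) Reconcile sections 2.4.1 and 2.6 to one primary model with three groups.

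(d) Delete the result statements in the Discussion or rewrite them as hypotheses. If outcome data have been examined, say so and date the analysis plan.

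**Cost.** Items (c) and (d) are mainly wording. Items (a) and (b) are design decisions: fewer outcomes can carry a primary claim. If Holm is used over two contrasts, its first step is at 0.025. For 0.5 SD with 40 per arm, power falls from 60% to 48% without baseline adjustment. Adjustment raises the effective difference to 0.5 / √(1 − ρ²). At an assumed baseline correlation ρ of 0.5 this is 0.577, with 62% power; at 0.8 it is 0.833, with 92% power. Only the upper end of that range reaches the 90% stated in section 2.1.1.
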